# Sunset Without AIDS: protocol for a randomized controlled trial of a brief video-based intervention to improve the ability of AIDS prevention in elderly men

**DOI:** 10.1186/s13063-022-06069-3

**Published:** 2022-02-14

**Keywords:** Older men, AIDS prevention ability, Video-based intervention, IMB Skills Model

## Abstract

**Background:**

Although progress has been made in the prevention and treatment of HIV in China, there are still a considerable number of new infections annually, especially in older men. HIV health education for older men is urgently needed. Evidence-based, acceptable, and scalable interventions are urgently needed to increase their capacity to prevent HIV. We describe a trial protocol to evaluate the effectiveness of a brief video-based intervention targeting older men's knowledge of HIV prevention.

**Design:**

This study is a randomized controlled trial. The trial will be held in the residents’ activity centers of three communities.

**Methods:**

A total of 450 older men will be randomly divided into three groups (*Sunset Without AIDS* intervention group and two control groups) for 2 weeks. We will assess the feasibility and acceptability of intervention through interviews. The primary outcome includes changes in participants’ knowledge related to AIDS after 2 weeks intervention and 1, 3, and 6 months of follow-up. The secondary outcomes, e.g., changes in participants’ stigma attitude, risk behaviors attitude, and risk behaviors related to AIDS, will be respectively assessed 2 weeks, 1 month, 3 months, and 6 months after the second intervention.

**Discussion:**

*Sunset Without AIDS* may be an innovative way to help older men improve HIV prevention knowledge, fill the gap in video-based HIV prevention education for the older men in China, and gain experience of HIV education. This project will innovate the HIV education ideas of older men and enrich the theoretical research content of AIDS-related education of older men. The findings may also provide the basis for the research and formulation of more reasonable AIDS education strategies, prevention, and control policies for the elderly.

**Trial registration:**

Chinese Clinical Trial Registry ChiCTR2100045708. Registered on 23 April 2021

## Introduction

The AIDS epidemic among older people in China has increased, and the number of new infections has continued to rise. At the beginning of 2017, in China’s 13th Five-Year Action Plan for AIDS Control and Prevention, older people were included in the key education groups for the first time [2]. According to data released by the Chinese Center for Disease Control AIDS, case reports for men over age 60 rose from 8391 in 2012 to 19,815 cases in 2017 [3] and 24465 cases in 2018 [4]. According to the World Health Organization Official WeChat figures released on December 1, 2020, the number of newly diagnosed HIV-infected persons aged 60 and above reported in China in 2019 was approximately 37000, and more than 100 cases were reported daily. This accounted for 25% of the total number of newly reported HIV infected persons. Infected males aged < 60 accounted for 77% of newly reports [5].

The main way of HIV infection in older people in China is sexual transmission, and the imbalance of sexual demand is one of the causes of HIV infection in older people [6]. Studies showed that adults older than 50 years old remain sexually active. Moreover, high-risk sexual behaviors such as having multiple sexual partners and unprotected sex activities with non-mating partners are common in the older population [7]. The survey found that up to 80% of infected older men admitted to having visited prostitutes, while older women were more likely to be infected within marriage [8]. A survey showed that 94.7% of older men infected with HIV never used condoms when having sex with a commercial partner [9]. This shows that older men have a low degree of understanding of safe sex and not notice taking protective measures when having sex with strangers, so they are at risk of infection and transmission of HIV [7]. In addition, for many older men infected with HIV, due to insufficient HIV-related knowledge, traditional sexual concepts, social discrimination, and other existence, they often do not carry out a timely HIV test or treatment and disclosure to their partners or family members. Therefore, it is necessary to educate older men about HIV-related risky sex and improve the AIDS prevention capabilities.

Developing countries represented by China have problems with HIV prevention education, such as outdated education models, poor effect of health education, and uneven distribution of educational resources [10, 11]. Because the literacy level of older people is generally low, it is difficult for them to acquire the correct knowledge of disease prevention. Under the influence of traditional culture, older people generally avoid talking about sex. Therefore, it is also difficult for us to really understand the changes of sexual physiology and psychology of older people. There is an urgent need to develop innovative HIV education model and improve the educational effect, which can be effectively implemented in over-burdened health systems. Video-based interventions are a promising but underused way to address these issues.

As a kind of teaching media, video interventions can deliver standardized messages. At the same time, messages can be woven into engaging storylines, piloted to ensure cultural relevance, and delivered at critical teachable moments [12]. They enrich the integration of education and entertainment. In recent years, some randomized controlled trials conducted in the USA and Africa targeting HIV infected people and high-risk populations. They have found that video-based interventions had a strong track record in improving health knowledge, increasing treatment adherence, promoting HIV screening and reducing sexual partners, supporting partner disclosure, and fostering attitude and behavior change [13–19]. However, there are few evidence-based studies on HIV educational video intervention in China, especially randomized controlled trials to evaluate the effects of video-based intervention to older men.

In recognizing that evidence-based, accessible, and scalable interventions to improve the ability of older men to prevent HIV are critical, our team developed a brief video-based intervention. Below, we describe the protocol of our randomized controlled trial to evaluate its effectiveness to improve older men’s HIV prevention ability in China. This intervention, called *Sunset Without AIDS*, is a 2-week experiment and includes components designed to increase HIV-related knowledge, improve HIV prevention motivation, and strengthen AIDS prevention behaviors among older men.

## *Sunset Without AIDS* overview

### Theoretical framework

In conceptualizing the video, the Information-Motivation- Behavioral Skills Model (IMB Skills Model) was selected. It was based on models which demonstrated the ability to promote behavior change in HIV/STD interventions. This model framework involves three aspects: AIDS-related information, motivation, and behavior skills [20]. *Sunset Without AIDS* includes all components of the IMB model and integrates other evidence-based video techniques to promote behavior change such as video modeling (visual and active demonstrations of desired behaviors) and gain-framed messaging. The combination of *Sunset Without AIDS* and IMB model is shown in Table 1.

**Table 1 Tab1:** Content of *Sunset Without AIDS* mapped to the IMB concept framework

Component	Story content (18 min)	Expert guidance content (7 min)
Information	The different ways by which the protagonists was infected with HIV and its performance if infected with HIV The older infected with HIV bring many troubles and problems to their families Addressing the misconceptions of AIDS discrimination	Experts provide HIV-related knowledge, attitude, and behavior guidance
Motivation	Avoiding high-risk sexual behaviors will benefit for individuals, partners, and families, thus increasing the motivation to prevent infection The real-life images and characters in the videos (the protagonists are all older) can effectively increase the motivation of older men to watch and learn Positively frames autonomy to facilitate partner disclosure and to seek social support	Analyze the focus issues in the video to strengthen relevant knowledge and behavior training Reiterates key messages using pictures and text to further motivate older men to turn avoiding infection into intrinsic motivation
Behavioral	Protagonist models facing life actively and became AIDS volunteers to contribute their strength to the society	Experts guide on how to avoid infection, such as the correct use of condoms Promotes problem solving to identify ways to reduce discrimination and develop solutions for cross-infection between partners and handle common situations that affect partner disclosure

### Video content development

*Sunset Without AIDS* was developed through an iterative multi-step process involving a team of people living with HIV (PLWH), clinicians, health workers, and other stakeholders. To improve the accuracy of the study, literature research, investigation, and interviews with older people (both male/females), Delphi’s expert consultation method was adopted to determine the educational core content of video design. The development of video content was through a community participatory approach, in-depth research and interviewed with older men and PLWH to ensure that the educational content was acceptable and compelling. Ultimately, the study advisory group identified three key areas that the intervention should target: increase HIV-related knowledge, improve HIV prevention motivation, and reduce high-risk sexual behaviors related to HIV among older men. Intervention video scrip was based on the true stories of old people infected with HIV. The script underwent iterative review and editing by the scriptwriter, until the expert advisory group felt the script addressed these issues in a compelling fashion.

The video was produced through a partnership with Creative Graphic Studio, a company with expertise in making health promotion videos. The result was a film, 25-min long, named *Sunset Without AIDS*. The characters in the video were all experienced actors, and they spoke in Chinese. *Sunset Without AIDS* consists of two parts: one is the story content of approximately 18 min. The other is expert guidance of approximately 7 min. The story content depicted a female protagonist, Li Li, 68 years old, who went to the hospital for examination because she had a cold for several months and did not get better. After being newly diagnosed with HIV, the film portrayed her in a series of complex psychological activities. The cause of her infection was traced to her husband Wang Yong, another 71-year-old protagonist who lost his sense of social existence and value after retirement. At the same time, Li Li often refused to meet her husband’s sexual needs, and the husband believed that he was no longer fertile. Under the egging of his neighbor (a lonely old man living alone), Wang Yong failed to refuse temptation and chose a low-priced prostitute to solve the loneliness. Wang Yong was infected with HIV through heterosexual contact outside marriage and illegal commercial sex without effective protection. Li Li was infected after having marital sex with her husband. At the end of the story, although Li Li and her husband experienced quarreling, complaining, and suffering, they faced the situation bravely with the help and support of their family. They not only received the treatment actively but also acted as volunteers to carry out AIDS health education for the older people around them. Expert introduction regarding HIV-related knowledge, attitude, and behavior guidance was followed at the end of video.

In the *Sunset Without AIDS*, the video provides information about the main route of infection in the older population, the importance of HIV prevention, and the education on HIV testing and treatment. Older men can watch the whole process of HIV infection through this brief video and perceive the risk of AIDS and the severity of the disease, thereby learning knowledge and skills, increasing awareness of AIDS prevention, and reducing risky behaviors (Figs. 1, 2, and 3).

**Fig. 1 Fig1:**
[figure not shown]
*Sunset Without AIDS*

**Fig. 2 Fig2:**
[figure not shown]
The story content of *Sunset Without AIDS*

**Fig. 3 Fig3:**
[figure not shown]
The expert guidance content of *Sunset Without AIDS*

### Aim/objectives

The aim of the study was to evaluate the effect of *Sunset Without AIDS* intervention on improving the ability of HIV prevention in older men. The primary objectives include the following: (1) raising awareness of HIV, (2) reducing HIV-related stigma, and (3) reducing HIV-related risk behaviors.

## Methods/design

Four hundred and fifty participants will be allocated to one of the three randomized groups after completing a baseline survey. Baseline assessments last approximately 30 min and include demographic items, HIV-related knowledge items, HIV-related stigma attitude items, HIV-related behaviors attitude items, and HIV-related behaviors items. At the same time, the acceptability and the method to acquire relating knowledge of HIV prevention will be evaluated through face-to-face interviews with participants.

To reduce contamination, the three groups will be from separate areas. Four follow-up visit assessments are expected at 2 weeks later, 1 month, 3 months, and 6 months. Our hypotheses are as follows: (1) compared with older men in the control groups, those in the *Sunset Without AIDS* intervention group will have a deeper awareness of HIV, less HIV-related stigma, and fewer HIV-related risk behaviors; (2) in comparison between the *Sunset Without AIDS* intervention group and normal video group, the former group integrated various knowledge and behavioral skills into the story. So, it will have better acceptability and feasibility on HIV prevention. Figure 4 shows the study flowchart.

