### Recruitment of participants

We will recruit 450 older men in multiple communities through on-site recruitment. In order to keep the baseline consistent, we have purposefully pre-selected three towns, Fangshan, Jiangbei, and Kuangchang. They are the most representative and have basically the same economic, cultural, and population levels in Luzhou city. In Chinese administrative divisions, each town contains 10–20 communities. In order to facilitate the implementation of intervention, two or three communities will be selected using simple random sampling from each town, and a total of 150 older men will be recruited from these communities in one town. The trial will be held in the residents’ activity centers of three communities (Fangshan community of Fangshan Town, Kuangchang community of Kuangchang town, and Jiangbei community of Jiangbei town).

Participants who sign up will be screened; for those who meet the inclusion criteria, we will issue informed consent to them and inform them in detail of the study purpose and process, number of participants, study duration, potential risks and benefits, random allocation, data confidentiality, etc. All information and written notices will be in Chinese. When the participants agree to join in the research and complete the follow-up measurement, an informed consent form will be signed for confirmation. If the participant is unable to read, the staff will read the informed consent to the participant in full and the participant will mark his or her own fingerprint to express consent; the entire process must be witnessed by a third party not involved in the trial.

To be eligible for trial participation, individuals must meet all the following inclusion criteria:
Male aged over 60 years oldClear consciousness, no mental illness and serious visual impairment, have certain reading ability and language expression abilityPlans to stay in the trial catchment area for over 6 months

Exclusion criteria include any of the following:
Ongoing or already on HIV education interventionCognitive and mental impairment and inability to communicate properlyImpaired vision or blind

The drop out criteria includes any of the following:
Have a serious illness during the experimentDeathOther irresistible factors, for example, infectious disease isolation

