### Randomization and allocation concealment

Individual randomization will be used in allocation. Participants will be randomly assigned to one of the three intervention groups on a 1:1:1 basis. Opaque envelopes will be prepared for randomization. In 450 envelopes, each will contain a note with the words “*Sunset Without AIDS* intervention group” or “Normal video group” or “Lecture group” (150 envelopes per group). A statistician will be responsible for the generation of random sequence numbers and place them on a sequential list that will be maintained by the trial coordinator. Participants (*n* = 450) will be randomly assigned a computer-generated random number from 1 to 450, and they will randomly select an envelope in the numbering order. For each envelope selected by participants, the total number of envelopes will be reduced by one until all 450 are achieved. Participants will be randomly allocated to the different groups with a closed envelope and supervise from a third party. Separate research staff will record the allocation information of the participants. Another staff will assign participants to interventions. These staff members were not involved in the data collection and analysis process. The data analysts are blinded to the allocation. All interviewers are not involved in delivering the intervention, so they will also remain blinded.

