### Contamination and intervention fidelity

To help ensure intervention fidelity and reduce contamination, we developed and revised multiple strategies. Some of the key strategies are listed in Table 2.

**Table 2 Tab2:** Key strategies to ensure intervention fidelity and reduce contamination

- Increased sample size up to 10% - The study group will discuss the types, scope and measures of reducing possible contamination sources through discussion and literature review - Training of trial staff and health workers to emphasize the effects of contamination. How to avoid it, how to use unbiased explanations to solve the problem - Different intervention groups will be delivered in separate areas - Intervention videos are kept by designated personnel and not available through other channels - Information packs with *Sunset Without AIDS* materials are clearly labeled and stored separately from normal video groups’ materials - Level and extent of participants reported contamination are measured at follow-up visits - Participants will be escorted before grouping and between survey locations - Field study team members confirm that trial participants only receive the specified intervention - Participants are randomly assigned to different groups by selecting envelopes - The data analysts are blinded to the allocation - Ensure that the educational content and duration of the video downloaded from the website of the Chinese CDC is the same as that of *Sunset Without AIDS* - Lecture group will be conduct by an AIDS expert for the same amount of time and content as the intervention group - Intervention sessions audio recorded, and 10% reviewed centrally [23] - All trial investigators will remain blinded	

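### The article says both that the three arms come from separate areas and that men are individually randomised from one pool; if arm follows town, arm and town cannot be separated

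*Protocol article*

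**What the plan says.** Four places in the protocol article bear on how men reach an arm.

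- **Methods/design:** "To reduce contamination, the three groups will be from separate areas".
- **Recruitment of participants:** "we have purposefully pre-selected three towns, Fangshan, Jiangbei, and Kuangchang". Within these, "two or three communities will be selected using simple random sampling from each town". The recruitment target is set town by town: "a total of 150 older men will be recruited from these communities in one town". Three activity centres are named as venues, one in each town.
- **Randomization and allocation concealment:** "Individual randomization will be used in allocation", and "Participants will be randomly assigned to one of the three intervention groups on a 1:1:1 basis". There are 450 envelopes in one pool ("150 envelopes per group"). No division of the pool by town is stated.
- **Contamination and intervention fidelity, Table 2:** "Different intervention groups will be delivered in separate areas". The same table also lists random assignment by envelope.

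Statistical analyses plans chi-square tests across the three arms for knowledge, behaviour attitude and behaviours, and ANOVA for stigma. It adjusts for baseline scores and applies a Bonferroni correction, with significance at 0.05. It states no term for town.

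**The concern.** The Methods/design sentence describes where the groups come from. The only areas the article describes are the three towns, and the 150 men recruited in each equal the size of one arm. Read together, these sections suggest one arm per town. The randomisation section describes something different: the envelope decides the arm, whatever the man's town.

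The choice between the two decides what kind of study this is. Under individual randomisation it compares 450 randomised men. With one arm per town it compares three purposively chosen towns, and any difference between them in schooling, local HIV campaigns, staff or lecturer is counted as an effect of the video. The statement that the towns are broadly alike does not remove this. Nor does adjustment for baseline scores, because whatever differs between towns after baseline stays tied to arm.

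**Working it through.** **1. The plan's own sample size.** Sample size and adherence gives 135 per group for 80% power, raised to 150. The 135 cannot be reproduced, because no effect size is given. The step to 150 agrees with a 10% allowance: 135 / (1 − 0.10) = 150. The article attributes the increase to attrition and secondary outcomes, and Table 2 mentions an increase of up to 10%. Neither place mentions an allowance for clustering by town.

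**2. Can both schemes hold?** With one pool of 450 envelopes and 150 men per town, the expected number of men of a given arm in a given town is 150 × 150/450 = 50. The chance that the draws put each arm wholly in one town is effectively zero. So if the envelopes decide the arm, the arms do not come from separate towns. If the town decides the arm, the envelopes do nothing.

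**3. What follows if arm = town.** There are three towns and three arm means, leaving 3 − 3 = 0 degrees of freedom for between-town variance. No analysis in the plan can then separate arm from town.

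The size can be illustrated with m = 150 men per town and an assumed intraclass correlation (ICC), since the article gives none:

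- Design effect: DE = 1 + (m − 1) × ICC
- True type I error of the three-arm test at 0.05: P(χ² with 2 df > 5.991/DE)
- True type I error of a two-sided pairwise test at 0.05: 2 × [1 − Φ(1.96/√DE)]
- Effective number per arm: 150/DE

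| Assumed ICC | DE | Three-arm error | Pairwise error | Effective n per arm |
|---|---|---|---|---|
| 0.005 | 1.745 | 18% | 14% | 86 |
| 0.01 | 2.49 | 30% | 21% | 60 |
| 0.02 | 3.98 | 47% | 33% | 38 |
| 0.05 | 8.45 | 70% | 50% | 18 |

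For example, at ICC 0.01, DE = 1 + 149 × 0.01 = 2.49. The three-arm error is P(χ² with 2 df > 5.991/2.49 = 2.41) = 30%. The pairwise error is 2 × [1 − Φ(1.96/1.578)] = 21%.

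The article does not say how many comparisons its Bonferroni correction covers. If it covers three pairs (0.05/3 per test, critical value 2.394), the pairwise error at ICC 0.01 is 2 × [1 − Φ(2.394/1.578)] = 13%, against a nominal 1.7%.

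Recruiting more men per town would not repair this. As m grows, m/DE approaches 1/ICC, so the effective number per arm cannot exceed 100 at ICC 0.01 or 20 at ICC 0.05.

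**4. What follows if men are randomised within towns.** Each town supplies about 50 men to every arm, so a town effect falls equally on all arms. The design effect for town is about 1, and the sample size needs no change for town clustering.

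**The case against.** The strongest reply is that nowhere does the article say that area, town and arm coincide. Individual allocation is described in operational detail and repeated in Table 2, and Methods/design itself has men allocated after the baseline survey. The Table 2 line on separate areas concerns delivery, so it may mean only that men are randomised individually and then sent to arm-specific venues. The match of 150 per town with 150 per arm proves little, since 450 divided by three gives 150 either way. The flowchart, which might settle the matter, is not shown.

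Most of this stands. The Table 2 line is ambiguous and cannot be counted as a contradiction. It does not rescue the Methods/design sentence, which says where the groups are from. Nor does the article say that men travel to another town's centre, as arm-specific centres would require. Under the venue reading, arm would be tied to venue and session group, though not to town of residence.

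The error rates are also open to challenge. They rest on assumed ICCs, treat towns as a random sample although they were chosen to be alike, and at the pairwise level depend on what the Bonferroni correction covers. That is fair, and it makes them illustrations.

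A reader might also infer that the analysis is invalid even under individual randomisation, because neither allocation nor analysis mentions town. The document does not support that. With a town design effect of about 1, a town term is then a matter of efficiency, and model terms of this kind are commonly left to the analysis plan.

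**Conclusion.** The contradiction between Methods/design, read with Recruitment of participants, and the randomisation section is in the text and must be resolved, because it decides whether the trial can attribute a difference to the video.

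The consequence is conditional. If arm follows town, there is one cluster per arm, arm and town are fully aliased, and the nominal 5% error rate is lost. With 150 men per arm and assumed ICCs of 0.005 to 0.05, the three-arm error would run from about 18% to 70%. At ICC 0.01 the pairwise error would be about 21% at 0.05 per test, or about 13% if Bonferroni covers three pairs. If men are randomised within towns, none of this applies.

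A reader might infer that the trial did assign one town per arm, or that these figures are its actual error rates. The document establishes neither. What it establishes is two incompatible descriptions of allocation.

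**What to change.** Reconcile Methods/design, Recruitment of participants, the randomisation section and Table 2:

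- Keep individual randomisation and delete the sentence "To reduce contamination, the three groups will be from separate areas".
- State that each town contributes men to all three arms.
- Say in Table 2 what separate areas means, and separate the arms within a town by room or session time.
- If allocation is not complete, use town as a stratum. Otherwise include town as a covariate in the analysis. Trial status gives enrolment from June 2021 with recruitment due to finish in December 2021, before the article appeared in February 2022, so the covariate is the likelier route.

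If enrolment in fact placed one arm per town, withdraw the individual-randomisation statement, report a three-cluster comparison in which arm and town are confounded, and drop confirmatory P-values.

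**Cost.** In the first case the cost is wording and one stratum or model term. Each town must run all three session types, and within-town contamination risk rises somewhat, although contamination is already measured at follow-up. In the fallback case the trial loses its confirmatory claim.
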